### Adherence and participant retention

2.8

Adherence is a vital aspect in studies on lifestyle interventions that entail a significant degree of intricacy and impact on the social and familial structure functioning of participants. CITA GO-ON implements specific strategies to promote adherence. During the randomization phase, the study coordinator conducts a face-to-face or telephone/virtual interview with each MD-Int participant to explain all study activities, identify potential obstacles for compliance with programmed interventions and assessments, and schedule workshops and activities. Each participant is provided with a paper form or virtual record of compliance with the intervention activities and study contact information. Separate forms to account for adherence to cognitive intervention (attendance to workshops and completion of individual home exercises), socio-emotional (attendance to workshops and completion of individual home exercises), physical activities (self-reported completion of prescribed activities), risk factor control (attendance to follow-up visits), and dietary intervention (attendance to workshops) will be collected. This will allow separate analysis of the association of adherence to each intervention and efficacy. The group leader or study coordinator assesses this register at every follow-up visit. After each group session, time is dedicated to addressing any doubts, issues, or challenges the participants may have. Furthermore, group leaders review the group activity plan and schedule for subsequent study activities. The variables included in “Nutritional Evaluation I” and “Physical Activity & Exercise Evaluation I” are surrogate markers for self-reported adherence. In this sense, the Mediterranean Diet Adherence Screener, the MEDAS questionnaire, the SPPB, the 6 m walking speed test, cardiovascular factors (blood pressure), and body anthropometry, measured every 4 months, will help us understand if intervention activities are changing participants’ lifestyles and will help us detect nonadherence situations.

Participants are permitted to bring a close relative to the nutritional and show cooking group meetings, mainly if they are not responsible for preparing the daily meal menu at home cooking.

### Virtual tools

2.9

All participants are questioned about previous experience with digital tools, including video calls, electronic mail and messages, and social media. During workshops, participants are trained to participate in group video calls and using these virtual tools to prepare for the possibility of utilizing them. The goal is to provide the necessary tools to evaluate and interact with participants who may be unable to attend in-person study visits. In fact, a telematic mNTB version has been administered in a sample of 50 persons before the CITA GO-ON study kick-off and will be administered via video call if necessary.

Self-administered REDCap questionnaires, mail reminders, and phone calls are used to communicate with the participants. Intervention materials, such as recommendations, recorded workshops, and individual cognitive training materials, are available on a web storage service platform for the intervention group.

### Statistical considerations

2.10

#### Sample size

2.10.1

Sample size calculations were based on the FINGER trial (Ngandu et al., 2015) and GZ pilot study data (Tainta et al., 2024a). Accepting a significance level of 5% and a statistical power of 90% in a one-sided test, 584 subjects would be necessary for each group, with a total of 1,096 participants, to detect a statistically significant difference between the two proportions of participants who decline in performance on the mNTB after 2 years, 49% for the RHA group and 32% for the MI group. The sample size has been calculated to allow a predicted 20% dropout rate according to the GZ study data. In the same way, considering the same level of significance, statistical power, and dropout rate, in order to detect a decline in performance on the mNTB score after 2 years, considering data from the GOIZ ZAINDU Pilot study, we calculated that a sample size of 802 randomized participants would be sufficient to detect by a two tailed Student t test, a difference between groups of 0.10 units in global mNTB score change, considering a 0.33 standard deviation.

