### Study objectives

2.2

The primary objective is to ascertain the efficacy of the intervention to attain a 20% reduction in the proportion of subjects exhibiting a decline in cognitive performance, as measured by the change in the global cognition z-score on the modified Neuropsychological Test Battery (mNTB) (Harrison et al., 2007; Kivipelto et al., 2013), between baseline and 24 month visits in the multidomain intervention group (MD-Int) relative to the regular health advice (RHA) group. Secondary objectives include: (1) analyzing the cost-effectiveness of the intervention; (2) determining the beneficial effects of the intervention on functional abilities, quality of life, and symptoms of depression and anxiety; and (3) investigating the impact of lifestyle interventions on: neuroimaging parameters of brain volumetry, white matter integrity and vascular burden; plasma biomarkers of Alzheimer’s pathology, neurodegeneration, and neuroinflammation; epigenetic marks; lipid dysregulation; and cognitive and brain reserve capacity.

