#### Allocation

2.10.2

Randomization list is created to follow a 1:1 ratio stratified by age, sex, and presence of mild cognitive impairment (MCI). To minimize bias, the allocation of participants to each group will be concealed through the REDCap randomization procedure, previous to the recruitment process begins. A member of the research team who will not carry out primary outcome assessments will enter participant details into the randomization system and inform relevant parties of the outcome of group allocation. The study participants are distributed in 4 waves of approximately 250 subjects, in which age, sex, and cognitive status are equally similarly distributed. As the distribution of those variables would be unknown at the time the randomization list is created, the resulting groups could have minimum size differences.

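### The primary sample-size statement contradicts itself: 584 per group is not 1,096 in total, the printed rates need only about 177 per group, and they do not match the 20% objective

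*Protocol article*

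**What the plan says.** All the planning figures for the comparison of proportions stand in the Sample size section (2.10.1) of the protocol article.

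- **Error rates:** "Accepting a significance level of 5% and a statistical power of 90% in a one-sided test".
- **Size:** "584 subjects would be necessary for each group, with a total of 1,096 participants".
- **Assumed proportions declining on the mNTB at two years:** "49% for the RHA group and 32% for the MI group".
- **Attrition:** "The sample size has been calculated to allow a predicted 20% dropout rate according to the GZ study data".

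The Allocation section (2.10.2) adds the ratio: "Randomization list is created to follow a 1:1 ratio". The Study objectives section (2.2) gives the target effect: the intervention is to "attain a 20% reduction in the proportion of subjects exhibiting a decline in cognitive performance". It does not say whether the 20% is relative or absolute.

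**The concern.** The per-group number and the total stand in one sentence and do not agree. The two rates, put through any usual two-proportion formula with the stated error rates and dropout, give a trial about a third of the stated size. The effect that they describe is also not the one named in the primary objective.

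These are the figures from which readers will judge the trial's sensitivity. Taken as printed, the trial looks for a 17-point difference with almost certain power, and a null result would seem to rule out effects much smaller than 17 points. If it was in fact sized for about 10 points, 90% power leaves no slack and a null result means something different. Any updated power statement has the same problem. The Results section reports 1,051 selected and 465 + 455 = 920 allocated at the time of writing, both below 1,096. Whether such a shortfall matters depends on which effect was planned.

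**Working it through.** **Inputs.** Section 2.10.1: one-sided alpha 0.05 (z = 1.645), power 0.90 (z = 1.282), p1 = 0.49, p2 = 0.32, dropout 0.20 already included in the stated size. Section 2.10.2: 1:1 allocation. Section 2.2: 20% reduction.

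**Step 1. Per-group number against total.** 2 × 584 = 1,168. The stated total is 1,096, and 1,096 / 2 = 548. The gap is 72. Equal allocation rules out unequal arms as the reason, and the one dropout allowance covers the whole statement.

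**Step 2. Size from the printed rates.** Two-proportion formula with pooled variance under the null, where p̄ = (p1 + p2)/2:

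n per group = [1.645 × √(2p̄(1 − p̄)) + 1.282 × √(p1(1 − p1) + p2(1 − p2))]² / (p1 − p2)²

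- p̄ = 0.405; √(2 × 0.405 × 0.595) = 0.6942; √(0.2499 + 0.2176) = 0.6837.
- n = (1.1419 + 0.8762)² / 0.17² = 140.9, so 141 evaluable per group.
- Dropout: 141 / 0.80 = 176.25, so 177 randomised per group and 354 in total.
- Ratio: 1,096 / 354 = 3.1.

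Variants for 49% versus 32%, per group:

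| Variant | Evaluable | After 20% dropout |
|---|---|---|
| One-sided, pooled, 90% (as stated) | 141 | 177 |
| One-sided, continuity correction, 90% | 153 | 192 |
| Two-sided, pooled, 90% | 174 | 218 (436 in total) |
| Two-sided, continuity correction, 90% | 185 | 232 |
| Two-sided, continuity correction, 95% | 226 | 283 |

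Unpooled variance (139 one-sided, 170 two-sided) and the arcsine method (142 and 174) change little. Nothing comes near 548 or 584.

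**Step 3. Power at the stated total.** 1,096 × 0.80 / 2 = 438 evaluable per group. For 49% versus 32%, one-sided 5%, power is 0.9998, not 0.90.

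**Step 4. Printed effect against the objective.** 0.49 − 0.32 = 0.17, and 0.17 / 0.49 = 34.7%. A 20% relative reduction from 49% is 0.49 × 0.80 = 39.2%. A 20-point absolute reduction is 29%. The printed 32% is neither.

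**Step 5. Which effect gives 1,096?** Same formula, alpha, sidedness, power and dropout:

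- 49% versus 39.2%: (1.1550 + 0.8955)² / 0.098² = 437.8, so 438 evaluable; 438 / 0.80 = 547.5, so 548 randomised per group; 2 × 548 = **1,096**.
- 49% versus 39%: 421 evaluable, 527 per group, 1,054 in total.
- 49% versus 40%: 521 evaluable, 652 per group, 1,304 in total.
- 49% versus 29% (absolute reading): 100 evaluable, 125 per group, 250 in total.

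The relative reading of the objective, applied to the printed 49%, returns the stated total exactly. The per-group figure of 548 differs from the printed 584 only in the order of its last two digits.

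**Step 6. What depends on the answer.** One-sided power after 20% dropout:

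| Randomised | 49% v 32% | 49% v 39.2% |
|---|---|---|
| 1,096 | 99.98% | 90% |
| 1,051 | 99.97% | 89% |
| 920 (if that were final) | 99.9% | 85% |

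**The case against.** The best counter-argument accepts the inconsistency and attacks the diagnosis. Having seen step 5, a reader might infer that the design effect is established as 49% versus 39.2%, that 32% and 584 are simply misprints, and that the trial was built for 9.8 points. The article does not support that as fact.

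- It prints none of 39.2%, 438 or 548. All three come from working back from the total.
- Section 2.2 does not call its 20% relative.
- Matching the total is not unique. With the same alpha, sidedness, power and dropout, 34% versus 25% also gives 548 per group, and so does 48% versus 38% with continuity correction. Neither uses the printed 49% or a 20% relative reduction, so both are less plausible, but they show that a match is not proof.
- The match depends on the formula. For 49% versus 39.2%, unpooled variance gives 545 per group after dropout, arcsine 549 and continuity correction 573.
- The rates are said to rest on the FINGER trial and the pilot study, whose data are not in the article. The 32% could be a misprint, an observed rate quoted beside a more cautious planning effect, or a real planning value with a wrong size.

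All of this stands, and it limits the explanation to a probable one. It does not touch steps 1 to 4, which use printed figures only.

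It can also be said that recruitment is complete and that on the likely reading the total is right, so no analysis or type I error changes. That is correct. It limits the consequence to how the trial's sensitivity is stated and read.

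**Conclusion.** The sample-size statement is wrong as written, in three ways that do not depend on how the error arose:

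1. 584 per group gives 1,168, not 1,096.
2. The printed rates need 177 randomised per group (354 in total; 436 if two-sided), so 1,096 is about 3.1 times the requirement and would carry 99.98% power instead of 90%.
3. A fall of 17 points, or 34.7% relative, agrees with neither reading of the 20% objective.

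Confidence in these is high. They rest on the stated alpha, sidedness, power, dropout and 1:1 ratio, and no standard variant rescues them.

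The explanation that the trial was planned on 49% versus 39.2%, with 548 per group, is the most probable one but needs the sponsor's confirmation. It assumes that the 20% is relative and that a pooled-variance formula without continuity correction was used.

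A reader might also infer from the factor of 3.1 that the trial is heavily oversized. The article does not support that either, because the factor holds only if 32% really was the planning rate, and the agreement in step 5 points the other way.

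**What to change.** Recover the original calculation. Then restate in section 2.10.1 the two rates, the evaluable and randomised numbers per group, the total and the power so that they agree with each other and with section 2.2. State in section 2.2 whether the 20% is relative or absolute.

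- **If the reconstruction is confirmed:** print 49% versus 39.2%, one-sided 5%, 90% power, 438 evaluable and 548 randomised per group after 20% dropout, 1,096 in total.
- **If 32% was the planning value:** give the power that it yields at the stated total (above 99%), correct the per-group number, and bring the 20% in the objective into line.
- **If the record shows something else:** report those inputs, with the method used.

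The cost is one corrected paragraph and a clarified objective, by erratum and matching protocol wording. Recruitment, allocation, assessments and analysis stay as they are. The last visit is expected in autumn 2026, so the correction can be made before results are known.

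### The 802 randomised stated for the continuous global mNTB outcome does not follow from its printed inputs, which give 574 to 576; at least one printed figure is wrong, and the protocol does not show which

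*Protocol article*

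**What the plan says.** Section 2.10.1 of the protocol article gives two sample size calculations. The first compares proportions of decliners and sets the error rates: "Accepting a significance level of 5% and a statistical power of 90% in a one-sided test". It also sets the attrition allowance: "The sample size has been calculated to allow a predicted 20% dropout rate according to the GZ study data".

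The second concerns the continuous global mNTB score. It carries those settings over ("considering the same level of significance, statistical power, and dropout rate") and states that "a sample size of 802 randomized participants would be sufficient to detect by a two tailed Student t test" the following effect: "a difference between groups of 0.10 units in global mNTB score change, considering a 0.33 standard deviation". Section 2.10.2 (Allocation) gives a 1:1 ratio. All inputs to the second calculation are therefore printed.

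**The concern.** A two-group t test with a standardised difference of 0.10/0.33, about 0.30, at two-sided 5% and 90% power needs roughly 230 per group. Even with 20% dropout, that falls well short of 401 randomised per group.

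The sentence matters because it is the only power statement in the article for the continuous score. Section 2.6.1 and Table 2 make the global composite z-score the primary outcome, and section 2.10.5 plans mixed models of the mNTB scores. If the SD is misprinted, a reader takes the change score to be less variable than was planned for. If the SD and difference are right, the stated number overstates the need. Either way, a reader cannot tell what effect, variability and error rates the continuous analysis was planned on.

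**Working it through.** **Inputs** (sections 2.10.1 and 2.10.2): two-sided alpha 0.05 (z = 1.960); power 0.90 (z = 1.282); difference 0.10; SD 0.33; 1:1 allocation; 20% dropout.

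**Step 1: attempt to reproduce 802.** Evaluable per group:

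n = 2 × (1.960 + 1.282)² × (0.33/0.10)² = 2 × 10.51 × 10.89 ≈ 228.9, so 229.

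The exact noncentral-t solution is 229.8, so 230. With 20% dropout:

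- normal formula: 229/0.8 = 286.25, so 287 per group and 574 in total
- exact t: 230/0.8 = 287.5, so 288 per group and 576 in total

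802 is not reproduced: 802/574 = 1.40 and 802/576 = 1.39.

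**Step 2: other readings of the sentence, with difference 0.10 and SD 0.33 unless stated.**

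| Reading | Total randomised |
|---|---|
| One-sided 5%, 90% power | 468 |
| Two-sided 5%, 80% power | 428 |
| Two-sided 5%, 95% power | 710 |
| Dropout applied as n × 1.2 instead of n/0.8 | 550 |
| SD anywhere from 0.325 to 0.335 (rounding) | 556 to 590 |
| Difference 0.095 (rounding) | 636 |
| Inflated for a Mann–Whitney test (relative efficiency 0.955 to 0.864) | 600 to 664 |

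None comes near 802. Reading the carried-over 5% as one-sided moves the answer further away.

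**Step 3: what 802 delivers on the printed inputs.** Evaluable per group: 802 × 0.8/2 = 320.8.

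- Standardised effect over its standard error: 0.10/(0.33 × √(2/320.8)) = 3.838
- Power ≈ Φ(3.838 − 1.960) = Φ(1.878) ≈ 0.970 (exact t 0.969), against the stated 0.90

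**Step 4: which single change gives about 802.**

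| Changed input | Total randomised |
|---|---|
| SD 0.39 | 800 (normal); 2 × 320.6/0.8 = 801.5 (exact t, before rounding up) |
| Difference 0.085 / 0.084 | 794 / 814 |
| Power 97% | 806 |
| Two-sided alpha 0.01 | 814 |
| Dropout 43% | 804 |

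SD 0.39 is the closest match, but it is back-solved. The article gives no such figure.

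**Step 5: consequence at the number allocated so far.** The Results section reports 465 + 455 = 920 allocated. The article does not say this is final, so these figures are conditional on it. With 20% loss, 920 × 0.8/2 = 368 evaluable per group:

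- SD 0.33: 0.10/(0.33 × √(2/368)) = 4.111; power ≈ Φ(2.151) ≈ 98%
- SD 0.39: 0.10/(0.39 × √(2/368)) = 3.478; power ≈ Φ(1.518) ≈ 93.5%
- Largest SD that keeps 90% power: 0.10/(3.242 × √(2/368)) ≈ 0.42

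**The case against.** The best defence is that the sentence claims only sufficiency. On the printed inputs, 802 is more than sufficient, with about 97% power. It is also not the larger total that the article derives: the proportion calculation comes first and leads to 1,096, and the continuous calculation reads as a supplement. At 920 randomised with 20% loss, power for a 0.10 difference exceeds 90% at SD 0.33 and at SD 0.39. On this view no design decision changes.

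Most of that stands and limits the severity. It does not make the sentence right. The sentence ties 802 to 90% power, and the printed inputs do not give 90% power at 802.

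Three stronger readings are tempting, and the document supports none of them:

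- *The trial is underpowered for the continuous outcome.* The mismatch runs the other way if 0.10 and 0.33 are correct. If the SD is about 0.39, 802 is about right.
- *The planning SD was really 0.39.* This is inferred only from how well it fits. Other single changes, including to alpha or dropout, land close to 802, and the pilot data are not shown.
- *The 0.10 shift contradicts the 49% and 32% of the proportion calculation.* Converting a mean shift into a proportion of decliners needs a distribution for the change score, such as normal with a common SD, which the article does not state. Nor does it say that the two calculations target the same effect.

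**Conclusion.** The stated sample size is wrong as written. With two-sided 5%, 90% power, a difference of 0.10, SD 0.33, 1:1 allocation and 20% dropout, the total is 574 to 576 randomised, and 802 is about 40% above that. At least one of the total, SD, difference, power, alpha or dropout is misstated, and the document does not identify which.

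The conclusion assumes that the carried-over settings are those printed for the first calculation and that the SD of 0.33 is that of the change score in each group, as the sentence reads. The practical effect is modest: about 97% power at 802 on the printed inputs and, if 920 is the final number with 20% loss, 98% at SD 0.33 or 93.5% at SD 0.39. It is a should-fix correction to the planning basis of the continuous primary outcome. It is not evidence that the trial is too small.

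**What to change.** Retrieve the inputs actually used, starting with the pilot SD of the change in global mNTB score, and correct whichever printed figure does not fit:

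- If 0.10 and 0.33 are confirmed with the stated error rates and dropout, say that 576 randomised gives 90% power, or that 802 gives 97%.
- If 802 stands, print the SD, difference, power, alpha or dropout that produces it.

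State alpha and sidedness for this calculation in full, so that they are not carried over from a one-sided one. Then give power for the continuous outcome at the number actually randomised, using the confirmed SD.

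The cost is one lookup in the pilot data or the original calculation, and a one- or two-sentence correction. No design or analysis change follows from it. The last study visit is expected in autumn 2026, so it can be settled before follow-up is complete.

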#### Allocation

2.10.2

Randomization list is created to follow a 1:1 ratio stratified by age, sex, and presence of mild cognitive impairment (MCI). To minimize bias, the allocation of participants to each group will be concealed through the REDCap randomization procedure, previous to the recruitment process begins. A member of the research team who will not carry out primary outcome assessments will enter participant details into the randomization system and inform relevant parties of the outcome of group allocation. The study participants are distributed in 4 waves of approximately 250 subjects, in which age, sex, and cognitive status are equally similarly distributed. As the distribution of those variables would be unknown at the time the randomization list is created, the resulting groups could have minimum size differences.

#### Blinding

2.10.3

As with any other intervention studies on lifestyle habits, CITA Go On has limitations regarding the maintenance of masking of the group assigned to each participant. Nevertheless, participants are said in the randomization visit to be referred to Group 1 in the case of RHA and Group 2 in the case of MD-Int assignment. Therefore, participants are not actively told which group, intervention or control, they belong to. Blinded neuropsychologists perform the primary and secondary cognitive assessment, and participants are specifically requested to avoid discussing the intervention with the research staff and other participants. Primary outcome raters did not participate in any of the cognitive and socio-emotional intervention activities and have no access to randomization information in the database.

#### Data collection and management

2.10.4

Data is collected in a computerized database using an electronic Clinical Record Form (eCRF) record system based on REDCap (Harris et al., 2008, 2018). REDCap is a secure web-based software platform designed to support data capture for research studies.

